## Abstract

**Background:**

Due to ageing of the population the incidence of multimorbidity and polypharmacy is rising. Polypharmacy is a risk factor for medication-related (re)admission and therefore places a significant burden on the healthcare system. The reported incidence of medication-related (re)admissions varies widely due to the lack of a clear definition. Some medications are known to increase the risk for medication-related admission and are therefore published in the triggerlist of the Dutch guideline for Polypharmacy in older patients. Different interventions to support medication optimization have been studied to reduce medication-related (re)admissions. However, the optimal template of medication optimization is still unknown, which contributes to the large heterogeneity of their effect on hospital readmissions. Therefore, we implemented a clinical decision support system (CDSS) to optimize medication lists and investigate whether continuous use of a CDSS reduces the number of hospital readmissions in older patients, who previously have had an unplanned probably medication-related hospitalization.

**Methods:**

The CHECkUP study is a multicentre randomized study in older (≥60 years) patients with an unplanned hospitalization, polypharmacy (≥5 medications) and using at least two medications from the triggerlist, from Zuyderland Medical Centre and Maastricht University Medical Centre+ in the Netherlands. Patients will be randomized. The intervention consists of continuous (weekly) use of a CDSS, which generates a Medication Optimization Profile, which will be sent to the patient’s general practitioner and pharmacist. The control group will receive standard care. The primary outcome is hospital readmission within 1 year after study inclusion. Secondary outcomes are one-year mortality, number of emergency department visits, nursing home admissions, time to hospital readmissions and we will evaluate the quality of life and socio-economic status.

**Discussion:**

This study is expected to add evidence on the knowledge of medication optimization and whether use of a continuous CDSS ameliorates the risk of adverse outcomes in older patients, already at an increased risk of medication-related (re)admission. To our knowledge, this is the first large study, providing one-year follow-up data and reporting not only on quality of care indicators, but also on quality-of-life.

**Trial registration:**

The trial was registered in the Netherlands Trial Register on October 14, 2018, identifier: NL7449 (NTR7691). https://www.trialregister.nl/trial/7449.

**Supplementary Information:**

The online version contains supplementary material available at 10.1186/s12877-021-02723-8.

## Background

The population is ageing, leading to an increased incidence of multimorbidity and related polypharmacy [1]. Polypharmacy is a well-known risk factor for hospital (re)admissions, which can have detrimental effects on older patients and therefore are considered an important measure of quality of care [2]. As such, it is not surprising that a significant number of these hospital readmissions is directly medication-related and that medication-related hospital (re)admissions occur more frequently in older individuals [3, 4].

The incidence of both medication-related hospital admissions and readmissions varies widely, ranging from 0.5 to 19.3 and 0.09% to 64.0%, respectively [5]. Several explanations might be given for this wide range. First, there is lack of a clear definition of “medication-related hospital admission” and “medication-related hospital readmission”. Most definitions are based on the assumption that (re)admissions are directly related to problems around pharmacotherapy and are defined as (I) drug-related problems, such as drug-drug interactions, inappropriate drug use, sub- and supra-therapeutic dosage, and adverse drug reactions [3, 6]. Second, another explanation for the wide range in incidence of medication-related hospital (re)admissions might be the difference in time-at-risk of adverse outcome, i.e. the time between discharge after the first hospital admission and subsequent readmission in different studies. The follow-up time of these studies ranges from 30 days to 3 years and it is self-evident that the percentages of readmissions rise substantially when the follow-up time increases [6–12]. Third, medication-related (re)admissions are probably under recognized, especially in older patients who often tend to have an atypical presentation of illness.

While there is ongoing discussion and a clear definition about medication-related hospital (re)admissions is lacking, the Dutch multidisciplinary guideline for polypharmacy in older patients published the (so-called) triggerlist with clinical events (triggers) and often involved medications that are known to be associated with an increased risk of medication-related admissions [13]. As such, this list could serve as a guide whether to call a hospital (re)admission medication-related. Table 1 shows the triggerlist, which is compiled based on data from the HARM-, IPCI- and QUADRAT studies [14–17].

**Table 1 Tab1:** Triggerlist from the Dutch guideline “Polypharmacy in the older patient” [13]

Trigger (adverse clinical event)	Often involved medication
Fracture / fall	Psychotropic medication (falls)/ corticosteroids / antihypertensive drugs
Collapse / hypotension / dizziness	Cardiac medication (antihypertensive drugs and antiarrhythmics)/ psychotropic medication
Bleeding (GI tract)/ supratherapeutic INR	Anticoagulants Antiplatelet drugs NSAID
Electrolyte imbalance / dehydration	Diuretics, ACEi, AII-blocker, NSAID, antidepressants
Renal insufficiency	ACEi, AII-blocker, NSAID
Hypo- or hyperglycaemia	Insulin/oral antidiabetics, Corticosteroids
Heart failure	NSAID
Obstipation / ileus	Opioids / calcium blockers
Vomiting / diarrhea	Antibiotics
Delirium / confusion / drowsiness	Psychotropic medication / cardiac medication / medication for micturition complaints / benzodiazepines

In order to reduce medication-related hospital (re)admissions, several interventions that involve medication review have been investigated. Although a recent systematic review showed that an isolated medication review had no effect on readmission rates, multiple studies claim the opposite by showing involvement of a pharmacist does lead to a reduction in readmission rates [18–21]. This discrepancy might be explained by the fact that medication reviews often are a part of more comprehensive interventions [22] and also that pharmacists do not just perform isolated medication reviews, but often (implicitly) combine it to a multifaceted program that includes medication reconciliation, patient counseling and adequate follow-up [23]. Nevertheless, these programs performed during admission are very time consuming, relatively expensive and the quality may vary considerably between pharmacists [21]. To overcome these problems a clinical decision support system (CDSS) that monitors medication and patient characteristics continuously and sends recommendations to general practitioners (GPs) and pharmacists after detecting a medication-related problem, could be used [24]. Consequently, possible medication-related problems will be detected immediately in contrast to manual medication reviews that are usually performed only once or twice a year. Currently available research on the continuous use of a CDSS mainly focuses on the inpatient (hospital and nursing home) setting [24–26]. As such, there exists a critical knowledge gap in the outpatient setting that needs to be addressed.

In view of the considerations above, the aim of this study is to investigate whether the continuous use of a CDSS decreases the number of hospital readmissions in older patients who previously have had an unplanned probably medication-related hospitalization according to the triggerlist from The Dutch multidisciplinary guideline for polypharmacy in older patients [13].

## Methods/design

### Study design and setting

The “Control in the Hospital by Extensive Clinical rules for Unplanned hospitalizations in older Patients” (CHECkUP) is a multicentre, prospective and randomized study. This study will be embedded in two hospitals namely Zuyderland Medical Centre (MC) (location Sittard-Geleen and location Heerlen) and Maastricht University Medical Centre + (MUMC+), The Netherlands. Zuyderland MC is a large teaching hospital and MUMC+ is an academic hospital. The patients will be randomized by block randomizations with a size of two. This study is blinded for patients as well as for the participating GPs and pharmacists.

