### Study procedures

Three times a week the electronic prescription system is used to select the patients of 60 years and older admitted to the hospital with polypharmacy and at least two medications from the triggerlist. A research nurse will visit the patient at the ward and assess whether the patient is eligible for inclusion. The patients will receive written information about the study and after 2 days the research nurse will visit them again. Then they have to indicate whether they are willing to participate by signing informed consent. Inclusion already started in April 2019 and will finish in August 2022.

After inclusion, patients will be randomized into the intervention or the control group by using a digital randomization system with block randomization. The randomization is blinded for the patients, the GP and the pharmacist. Figure 1 illustrates the study design and randomization procedure.

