### Questionnaires

All patients (both intervention and control group) will be sent standardized questionnaires about the quality of life (EuroQol 5D-5L (EQ-5D-5L)) and costs from a societal perspective (Resource Use Measurement (RUM)) at hospital discharge, and after 3, 6 and/or 12 months after inclusion [28, 29]. The research nurse will determine whether the included patient will receive the second RUM questionnaire at 3, 6 or 12 months after inclusion, in order to make sure that the groups are equal. The patients will receive the questionnaires via email and receive an automatically generated reminder after 1 week. The questionnaire must be completed within 1 month.

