### Data analysis / statistical analysis

The effect evaluation will be analyzed according to the intention to treat principle. The difference in primary and secondary outcome variables between the intervention and the control group will be assessed using mixed effect models to account for the clustering of patients within physician and/or repeated measurements. A logit link function will be used for the binary outcomes and an identify link for numerical outcomes. A likelihood-based approach will be applied to account for missing outcomes variables, assuming missingness at random (MAR). The stratification variable (hospital location), variables related to missing data/drop outs (to ensure MAR) and variables related to the outcome such as age and sex, will be included in the fixed part of the models.

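### A published block size of two, with inclusion still running, lets anyone who learns the first allocation of a pair know the second for certain

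*Protocol article*

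**What the plan says.** All references are to the protocol article.

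- **Study design and setting** gives the scheme: "The patients will be randomized by block randomizations with a size of two". One size is named, and no variation in size is mentioned.
- **Sample size calculation** plans 1200 patients per group, so allocation is 1:1 and each block holds one patient per arm.
- **Study procedures** gives the order of events: "After inclusion, patients will be randomized into the intervention or the control group by using a digital randomization system with block randomization". It gives the recruitment period: "Inclusion already started in April 2019 and will finish in August 2022". It also names the blinded parties: "The randomization is blinded for the patients, the GP and the pharmacist".
- The same section describes the enrolling role: "A research nurse will visit the patient at the ward and assess whether the patient is eligible for inclusion". The nurse returns after two days for the consent decision.
- **Intervention group** and **Control group** say that the medication optimization profile goes to the GP and pharmacist for intervention patients only. For controls one is generated at discharge but not sent.
- **Data analysis / statistical analysis** puts hospital location, age, sex and variables related to missing data into the fixed part of the models.

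**The concern.** Two is the smallest possible block at 1:1, and its sequence is the easiest to foresee. Randomizing through a digital system after consent hides the current patient's allocation. It does not stop someone who knows the previous allocation from deducing the next one before that patient is approached or consents.

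If a person with influence over who is enrolled, or in what order, had that knowledge, frailer or less cooperative patients could be brought forward or deferred according to the arm that is due. The arms would then differ at baseline, and the readmission comparison would carry that difference. Publishing the block size during recruitment removes the remaining uncertainty about how the sequence is built.

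**Working it through.** **Inputs.** Block size 2 (Study design and setting); 2400 patients, 1200 per group, and a target reduction in readmission from 20% to 15% (Sample size calculation). The article gives no predictability figure to reproduce.

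**Predictability with pairs.** The observer is assumed to know the block size and all earlier allocations in the sequence.

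- First of a pair: probability of a correct guess 0.5, never certain.
- Second of a pair: probability 1, always certain.
- Share certain = (0 + 1)/2 = 50%, which is 0.5 × 2400 = 1200 allocations.
- Share guessed correctly = (0.5 + 1)/2 = 75%.

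**Larger fixed blocks.** For size 4, position by position:

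- The four guessing probabilities are 1/2, 2/3, 2/3 and 1. Their mean is 2.833/4 = 70.8%.
- Position 4 is always certain. Position 3 is certain when the first two agree, which has probability 1/3. Share certain = (1/3 + 1)/4 = 33.3%.

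Exact enumeration in the same way gives sizes 6 and 8. The varying scheme was simulated, with the observer guessing the arm that is behind.

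| Scheme | Certain in advance | Guessed correctly |
|---|---|---|
| Fixed 2 | 50.0% | 75.0% |
| Fixed 4 | 33.3% | 70.8% |
| Fixed 6 | 25.0% | 68.3% |
| Fixed 8 | 20.0% | 66.6% |
| Random 4, 6, 8, undisclosed | about 0.2% | about 68% |

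The 0.2% counts only positions where the running imbalance has reached its maximum of four. I also simulated an observer who knows the set of sizes and uses the full history. About 2.3% of allocations are then certain and 68% are guessed correctly. Even in that case the certain share falls from 50% to about 2%.

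**What it could do to the result (illustration, not an estimate).** Suppose that in a fraction f of pairs the first allocation is known and acted on. Second-in-pair patients then have readmission risk shifted by d points, down in one arm and up in the other. Second-in-pair patients are half of each arm, so the arm means move by −f·d/2 and +f·d/2, and the difference is biased by f·d.

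- f = 1, d = 1 point: bias 1 point, one fifth of the 5-point target.
- f = 0.25, d = 1 point: bias 0.25 point, one twentieth of the target.

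The article gives neither f nor d, and f may be zero.

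**Which check would detect it in patients already enrolled.** Comparing all first with all second patients pools the arms. Second patients are sicker when one arm is due and healthier when the other is due, so the shifts cancel. With 1200 pairs and second patients shifted by ±0.15 SD according to arm, simulation gave rejection in about 5% of runs, which is only the false-positive rate. Comparing arms among second patients tests a difference of 0.30 SD with about 600 per arm: standard error √(2/600) = 0.058, z = 0.30/0.058 ≈ 5.2. It rejected in practically every run.

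**The case against.** The strongest reply is that exposure is not documented. A reader might infer that the research nurse is unblinded because the nurse is missing from the list of blinded parties. An article is a condensed account, and who may see the allocation is commonly left to the full protocol. That inference is not supported.

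A reader might also take the questionnaire text, "The research nurse will determine whether the included patient will receive the second RUM questionnaire at 3, 6 or 12 months after inclusion" followed by "in order to make sure that the groups are equal", as proof that the nurse works with knowledge of arm. The Economic evaluation section describes three random cohorts with about a third of participants at each time point. The more natural reading is that these cohorts are kept equal in size, which needs no knowledge of arm.

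Nor does "The stratification variable (hospital location" in the analysis section contradict the randomization text. The randomization text is silent on stratification, which is condensation, and the minimum of 300 patients per group per location fits allocation within location.

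Scope for steering is also limited. Candidates come from the prescription system three times a week; age, number of medications and trigger medications are objective; and life expectancy is judged by the involved practitioners. GPs and pharmacists see a profile arrive for an intervention patient but do not enrol. To say that no model could repair the bias would go too far, since the planned covariates reduce bias from selection on measured risk.

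What stands after all this is the block size itself. Some discretion remains in assessing ability to consent and in how and when patients are approached. If blocks run within location, the observer needs only the previous allocation at that location, and local research staff are the people best placed to have it.

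**Conclusion.** The point holds as a conditional design risk that rests on the stated block size. Half of all allocations are certain, and three quarters guessable, for an observer who knows every earlier allocation in the sequence. Both figures are upper bounds and shrink with incomplete knowledge. The article does not show that any enrolling person has that knowledge, or that selective enrolment has occurred. Any selection on frailty or cooperation that the covariates do not capture would remain after adjustment. The gain from changing the scheme lies mainly in removing certainty; the drop in guessability, from 75% to about 68%, is modest. The change is worth making because it is cheap and inclusion is still open.

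**What to change.** 1. **Remaining inclusions.** Complete any open pair, then set the randomization system to permuted blocks whose size varies at random (for example 4, 6 and 8) within hospital location. Do not disclose the sizes to recruiting staff or in publications while inclusion runs.
2. **Access.** State in the protocol that allocations are visible only to those who release the medication optimization profiles, and not to staff who assess eligibility or take consent. In the same edit, say that randomization is stratified by hospital location, if that is so.
3. **Patients already enrolled.** Using the allocation list, compare baseline risk between arms among second-in-pair patients, with the same comparison among first-in-pair patients as reference. Do not compare first with second patients pooled over arms.

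Cost: a configuration change, a protocol amendment of a few lines, and one descriptive table. The largest imbalance at any moment is half the largest block, 8/2 = 4 patients per location. If the three sites named in the article are separate strata, that is at most 3 × 4 = 12 of 2400, or 0.5%. The sample size calculation does not depend on block size and is unaffected.

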#### Secondary outcomes

The secondary outcomes of this study are (I) mortality within 1 year after study inclusion; (II) the number of emergency department visits; (III) the number of nursing home admissions; (IV) time to hospital readmission; and (V) the number of hospital readmissions after 30 and 180 days. Next, we will analyze whether the readmission is (probably) medication-related. Whether a hospital readmission is medication-related will be defined afterwards, using the triggerlist. The information for secondary outcomes will be obtained from the electronic prescription system and electronic patient record. Furthermore, quality of life (QoL) and costs measured from a societal perspective will be assessed at baseline (hospital discharge) and after 3, 6 and/or 12 months (see questionnaires).

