### Intervention group

Patients included in the intervention group will undergo continuous medication checks using the CDSS once the patient is discharged. At discharge, the GP and pharmacist will receive their patient’s MOP. From then on the MOPs will be sent on a weekly basis for the period of 1 year. The GPs and the pharmacists can access this MOP and make necessary changes to the medication when appropriate. When they decide not to follow the recommendation made by the CDSS they are asked to indicate a reason.

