### Control group

The control group will receive standard care. The GPs and the pharmacists are not informed of which patients are participating as control. Therefore the GPs and pharmacists are blinded for this part of the study. The CDSS will also generate a MOP at discharge for patients in the control group. However this will not be sent to the patient’s GP and pharmacist and is only generated for analysis at the end of the study.

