## Discussion

This study is expected to add evidence on the knowledge of medication optimization and whether continuous use of a CDSS ameliorates the risk of hospital readmission and other adverse outcomes in older patients who have already had an unplanned hospitalization.

Hospital (re)admissions place a significant burden on the healthcare system, with impact on quality of life from the patient perspective and being an important cost driver from the societal perspective. In earlier studies, different interventions have been investigated to reduce readmissions, but the results were inconclusive due to large heterogeneity in study designs and therefore their effect on hospital readmissions. As such, the optimal template of medication optimization is still unknown. This is the first study that includes patients with a high risk of having a medication-related admission based on the triggerlist. We deliberately chose to include all readmissions as primary outcome and not specifically medication-related readmissions because a clear definition is lacking. By using a suboptimal definition it is likely we would miss readmissions that later turn out to be medication-related.

To our knowledge, this is the first large randomized blinded study providing one-year follow-up data and reporting not only on quality of care indicators (readmissions), but also on quality-of-life and costs. This contrasts to other studies in the field, which usually have a follow up of 30 or 60 days at most. This is an important strength of our study, while we believe that in this population healthcare status and medication prescriptions alter frequently and a follow up of only 30 or 60 days is too short to identify all possible consequences and the time to the occurrence of adverse outcome might vary considerably. Another strength of this study is that it will be conducted in the outpatient setting and directly in daily clinical practice and therefore improves the possibility to implement the CDSS in the shortest possible notice. The inclusion of patients has already started in April 2019, but the patient inclusion was slower than expected due to different causes. The participation of GPs and pharmacists was lower than expected, we experienced several IT problems (not related to CDSS itself) that affected inclusion and from March 2020 we had to deal with the COVID-19 pandemic. As such, during many months the inclusion was discontinued.

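### The trial is declared blinded for GPs and pharmacists, but they know the allocation of every intervention patient from the first profile they receive; only control participation is hidden from them

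*Protocol article*

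**What the plan says.** Three places in the protocol article present the trial as blinded:

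- Study design and setting: "This study is blinded for patients as well as for the participating GPs and pharmacists".
- Study procedures: "The randomization is blinded for the patients, the GP and the pharmacist".
- Discussion: "this is the first large randomized blinded study providing one-year follow-up data".

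Two places describe what GPs and pharmacists actually see:

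- Intervention group: "At discharge, the GP and pharmacist will receive their patient’s MOP", followed by "From then on the MOPs will be sent on a weekly basis for the period of 1 year". They may change the medication in response, and "When they decide not to follow the recommendation made by the CDSS they are asked to indicate a reason".
- Control group: "The GPs and the pharmacists are not informed of which patients are participating as control". A profile is also generated for controls at discharge, but it is kept for the final analysis and not sent. That section then says the providers are blinded for this part of the study, a limit that the design section and the Discussion do not carry.

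**The concern.** GPs and pharmacists are the people through whom the intervention works. They cannot receive and act on a patient's profile without knowing that the patient is in the intervention arm. The design section nevertheless assigns them a blinding that the trial does not have for that arm.

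What is at stake is how the primary result is read. The primary outcome, any hospital readmission within one year, needs no judgement of cause. Its occurrence may still depend partly on primary-care decisions, such as how closely a patient is watched or whether a patient is referred. If a provider handles a flagged patient differently for reasons other than the content of the recommendations, the comparison picks that up as well. This can be acceptable in a pragmatic trial if it is reported plainly. A reader told that the trial is blinded for providers would discount performance bias more than the design allows.

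**Working it through.** The plan gives no figure on this point, so the check is a comparison of the sections.

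| Who | What the design section declares | What the arm descriptions provide | Do they agree? |
|---|---|---|---|
| GP and pharmacist, intervention patient | Blinded | Receive the patient's profile at discharge and weekly for one year; act on it; are asked for a reason if they do not follow it | No |
| GP and pharmacist, control patient | Blinded | No profile sent; control participation not disclosed | Yes |
| Patient, either arm | Blinded | Nothing that contradicts it | Yes, as far as the text goes |

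**Step 1: does a profile reveal the arm?** Profiles go to providers for intervention patients and are withheld for controls. Receipt of a profile therefore identifies the intervention arm with certainty.

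**Step 2: does the absence of a profile reveal the arm?** No. Control participants are not identified, so a GP who receives nothing for a patient cannot tell a control from someone outside the trial. This concealment is real.

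**Step 3: how many patients are concerned?** The Sample size calculation section plans 1,200 intervention patients out of 2,400, and 1,200 / 2,400 = 50%. The mismatch covers all of the intervention arm and none of the control arm.

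**Step 4: does the number of profiles matter?** Discharge plus weekly for a year is at most 1 + 52 = 53 per patient. This is a ceiling: the legend of Fig. 2 says recommendations go to the GP and/or pharmacist when a clinical rule applies, and that no further action is needed when none does. The count is not a measure of bias, because one profile already discloses the arm.

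**Step 5: can the declarations be read so that they agree?** The Study procedures sentence could be taken to refer to the act of randomization rather than to what follows. On that reading it is compatible with the arm descriptions. The design section speaks of the study as a whole and the Discussion labels the whole trial, so neither can be read that way.

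**The case against.** The strongest reply is that the article hides nothing. The Intervention group and Control group sections say openly who receives profiles, and the latter limits the provider blinding in so many words. A GP's response to a profile is the intervention itself, not a contamination of it. Withholding the identity of controls guards against compensatory care for them. No direction or size of bias has been shown, and the documents do not describe GP referral as the route to readmission.

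Much of this stands. It limits the point to a misstatement of the design and leaves any effect on readmission as a possibility. It does not rescue the unqualified sentence in the design section or the label in the Discussion, which a reader may well take at face value.

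Three stronger readings are tempting, and the documents do not support them:

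- **That the trial has no blinding at all.** Control participation is withheld from providers, and nothing contradicts the statement that patients are blinded.
- **That patients learn their arm through medication changes and that this colours their questionnaires.** No section says that a GP tells a patient that a change came from a profile. Medication also changes under standard care, and the Discussion itself notes frequent changes in this population.
- **That outcome classification is unprotected.** The primary outcome is any readmission and needs no classification of cause. Only the additional medication-related analysis does, and for it the article names an instrument: "Whether a hospital readmission is medication-related will be defined afterwards, using the triggerlist". The article does not say who classifies or whether they are masked, but a condensed article may leave that to the full protocol or analysis plan, so its absence here is not a finding.

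**Conclusion.** The point holds as a contradiction within the article. GPs and pharmacists are unblinded for every intervention patient from the first profile. The only blinding on the provider side is that control participants are not identified to them. The design section and the Discussion state more than this, and the Study procedures sentence should be made unambiguous.

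The extent is the whole intervention arm, half of the planned sample. The consequence for the readmission comparison cannot be quantified from the documents. That it could exist rests on the assumption that GPs or pharmacists have some influence on care that bears on readmission. The primary endpoint, its analysis and the sample size are unaffected. What changes is what may be claimed about performance bias. The correction should be made, because it is cheap and bears on how the main result is interpreted.

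**What to change.** Bring Study design and setting, Study procedures, Intervention group, Control group and Discussion into line with one description:

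- GPs and pharmacists are unblinded for intervention patients, for whom they receive profiles.
- Control participation is not disclosed to GPs and pharmacists.
- Patients are not told their allocation.

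In the Discussion, remove the unqualified word 'blinded' from the claim about the trial's novelty, or replace it with this description. Add a sentence acknowledging that providers' knowledge of the intervention arm could affect care that bears on readmission. Carry the same wording into the report of the results.

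The cost is editorial. Recruitment, the intervention, data collection, sample size and analysis stay as they are.
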